### **Low-calorie diet**

Subjects are recommended to consume 600 calories less every day, depending on their age, gender, activity levels and body weight. Guidelines for daily amounts are between 1200 and 1500 calories for women and between 1500 and 1800 calories for men.

According to local standards (Diabetes UK), subjects are advised to eat regularly every day (5 times/day), to control their portion sizes, and intake of carbohydrates/ starchy foods, to increase their intake of low glycaemic index (GI) and high protein foods, as well as vegetables, and to reduce their intake of foods high in fat, sugar, and alcohol.

### **Exercise advice**

Patients in both the EndoBarrier and control arms will be given the same advice to include more physical activity in their daily routine for example walk more every day, climb the stairs instead of taking the lift or escalators, walk to the next bus stop, walk to the shops, ride an exercise bike while watching TV. They will also be encouraged to do more activity in their leisure time such as going for a walk, cycle ride or swim with friends or family. They will be asked to start with short periods of low-intensity exercise and increase the intensity and duration slowly. Their goal will be to include 150 minutes (2 ½ hours) a week of moderate intensity and 75 minutes a week of vigorous intensity aerobic activity and muscle strengthening activities more than 2 days a week. Changes in physical activity level will be monitored using the International Physical Activity Questionnaire (IPAQ) at Dietetic follow up appointments. Tools such as pedometers will be used as a motivator to help individuals increasing their exercise. Any exercise will be adjusted to individual needs and activity levels.

### **Dietitian Follow up**

Patients in both the EndoBarrier and control arm will be seen for review by the study dietitian at visits 6, 7, 9, 11, 12, 13, and 15. Motivation, dietary compliance and the average daily level of physical activity will be recorded.

### **Telephone counselling**

In between visits at 5 days, 2, 4.5, 7.5, 10.5, 13.5, 16.5 and 19.5 months, (T1-8) subjects will be contacted by the dietitian or another researcher to assess patient's well-being and motivation on the trial. They will be also reminded to attend their next study visit.

|                                                                                   |                                                                             |                                    |                                               |                                            |
|-----------------------------------------------------------------------------------|-----------------------------------------------------------------------------|------------------------------------|-----------------------------------------------|--------------------------------------------|
| [figure not shown] | Title:
EndoBarrier TM
Gastrointestinal Liner
Diabetes Trial | Protocol No:
Version 5.0 | Sponsor:
Imperial College
London | Date:
5 th March 2018 |
|-----------------------------------------------------------------------------------|-----------------------------------------------------------------------------|------------------------------------|-----------------------------------------------|--------------------------------------------|

### 5.5.4 Medical history and physical examination

A medical history will be performed at the screening visit to record illnesses, disorders and medications. This information needs to be updated on all follow-up visits.

Physical examination will be performed at the Screening visit (study visit 1) according to local procedure. During this visit the doctor will perform a cardiology, respiratory and gastrointestinal examination on the patient. They may go on to examine other appropriate systems if clinically indicated.

Any abnormal, clinical significant findings must be recorded in the eCRF.

Any changes in subsequent visits as compared to the screening visit which fulfils the criteria of an AE must be recorded as an AE. Any changes in concomitant illness will be recorded as changes in medical history. Any changes in medications will be recorded in the eCRF.

### 5.5.5 ECG

An ECG will be performed at the screening visit. The ECG will be interpreted, signed and dated by the investigator before study visit 2.

The interpretation must follow the categories:

- Normal
- Abnormal, not clinically significant
- Abnormal, clinically significant

If the ECG is abnormal and clinically significant, then the subject will be sent for further investigations and if necessary treated prior to study entry. If the abnormality cannot be treated then they will not be able to enter the study.

### 5.5.6 Urine dipstick and pregnancy test

Urine dipstick tests will be performed at the screening visit to determine pathological changes (e.g. protein in urine and any evidence of infection) in patient's urine. Any abnormal, clinical significant findings must be recorded in the eCRF.

Female urine pregnancy tests will be performed for females of childbearing potential at screening and at any time during the trial if a menstrual period is missed.

Female patients of child bearing potential who take part in the EndoBarrier trial will have already been consented to confirm they have no intentions to get pregnant during the duration of the study period. The use of adequate contraceptive methods will also be reinforced to each individual at screening and during each study visit. In the unlikely event that a patient's pregnancy test comes

|                                                                                   |                                                                                                  |                                           |                                                             |                                                  |
|-----------------------------------------------------------------------------------|--------------------------------------------------------------------------------------------------|-------------------------------------------|-------------------------------------------------------------|--------------------------------------------------|
| [figure not shown] | Title:
EndoBarrier TM
Gastrointestinal Liner
Diabetes Trial | Protocol No:
Version 5.0 | Sponsor:
Imperial College
London | Date:
5th March 2018 |
|-----------------------------------------------------------------------------------|--------------------------------------------------------------------------------------------------|-------------------------------------------|-------------------------------------------------------------|--------------------------------------------------|

back positive the patient will be adequately advised regarding the pros and cons of removing the device at that time. Endoscopy is safe during pregnancy but we have no data regarding the safety profile of the EndoBarrier device or indeed its metabolic effects during pregnancy. We would therefore advise that in general, if a patient falls pregnant during the study, that the device is removed when it is safe to do so.

Pregnancy tests will not be required for females who have undergone a hysterectomy or bilateral tubal ligation, or for females above the age of 50, who have been without menstrual period for at least one year. Pregnancy tests will also be performed for all females in sub-group 1 prior to fMRI (visits 3 and 8).

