### 4.3 Exclusion criteria

1. Language barrier, mental incapacity, unwillingness or inability to understand and be able to complete questionnaires
2. Non-compliance with eligibility criteria
3. Females of childbearing potential who are pregnant, breast-feeding or intend to become pregnant or are not using adequate or reliable contraceptive methods
4. Evidence of absolute insulin deficiency as indicated by clinical assessment, a long duration of T2DM and a fasting plasma C-peptide of <333pmol/L
5. Current use of insulin
6. Previous diagnosis with Type 1 DM or a history of ketoacidosis
7. Requirement of NSAIDs (non-steroidal anti-inflammatory drugs) or prescription of anticoagulation therapy during the implant period
8. Current iron deficiency and/or iron deficiency anaemia
9. Symptomatic gallstones or kidney stones at the time of screening
10. History of coagulopathy, upper gastro-intestinal bleeding conditions such as oesophageal or gastric varices, congenital or acquired intestinal telangiectasia
11. Previous GI surgery that could affect the ability to place the device or the function of the implant
12. History or presence of active H. pylori (if subjects are randomised into the EndoBarrier arm and have a history or presence of active H. pylori – tested during study visit 2 - they can receive appropriate treatment and then subsequently enrol into the study)
13. Family history of a known diagnosis or pre-existing symptoms of systemic lupus erythematosus, scleroderma or other autoimmune connective tissue disorder
14. Severe liver impairment i.e. AST, ALT or gGT >4 times upper limit of the reference range or kidney impairment i.e. estimated Glomerular Filtration Rate (GFR) < 45 ml/min/1.73m^2
15. Severe depression, unstable emotional or psychological characteristics (indicated by Beck Depression Inventory II score >28)
16. Poor dentition and inability to adequately chew food
17. Planned holidays up to three months following the EndoBarrier Implant
18. Previous EndoBarrier implantation

|                                                                                   |                                                                                                  |                                           |                                                             |                                                  |

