**Table 2. Summary of study visit schedule**

| Activities                                              | Screening | Baseline    |             | Treatment   |             |             |             |             |             |               |             |               |             |                |                |              |                | Follow-up    |                |              |                |              |              |
|---------------------------------------------------------|-----------|-------------|-------------|-------------|-------------|-------------|-------------|-------------|-------------|---------------|-------------|---------------|-------------|----------------|----------------|--------------|----------------|--------------|----------------|--------------|----------------|--------------|--------------|
|                                                         | V1        | V2          | V3          | V4          | T1          | V5          | V6          | T2          | V7          | T3            | V8          | T4            | V9          | T5             | V10            | V11          | T6             | V12          | T7             | V13          | T8             | V14          | V15          |
| Week/ Month/Day                                         |           | - 4w
±7d | - 2w
±7d | - 0w
±3d | + 5d±
3d | + 10d
±3 | + 1m
±7d | + 2m
±7d | + 3m
±7d | + 4.5m
±7d | + 6m
±7d | + 7.5m
±7d | + 9m
±7d | + 10.5m
±7d | + 11.5m
±7d | + 12m
±7d | + 13.5m
±7d | + 15m
±7d | + 16.5m
±7d | + 18m
±7d | + 19.5m
±7d | + 23m
±7d | + 24m
±7d |
| Informed consent (5.1)                                  | X         |             |             |             |             |             |             |             |             |               |             |               |             |                |                |              |                |              |                |              |                |              |              |
| Inclusion & exclusion criteria (4.2, 4.3)               | X         |             |             |             |             |             |             |             |             |               |             |               |             |                |                |              |                |              |                |              |                |              |              |

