| Height (5.5.8)                                          | X         |             |             |             |             |             |             |             |             |               |             |               |             |                |                |              |                |              |                |              |                |              |              |
| Waist circumference (5.5.9)                             | X         | X           | X           | X           |             | X           | X           |             | X           |               | X           |               | X           |                | X              | X            |                | X            |                | X            |                | X            | X            |
| Routine blood tests (5.5.10)                            | X         |             | X           |             |             | X           | X           |             | X           |               | X           |               | X           |                | X              | X            |                | X            |                | X            |                | X            | X            |
| Urine dipstick and female pregnancy test (5.5.6)        | X         |             |             |             |             |             |             |             |             |               |             |               |             |                |                |              |                |              |                |              |                |              |              |
| Changes in medical history/medication (5.5.4)           |           | X           | X           | X           |             | X           | X           |             | X           |               | X           |               | X           |                | X              | X            |                | X            |                | X            |                | X            | X            |
| Randomisation (5.2)                                     |           | X           |             |             |             |             |             |             |             |               |             |               |             |                |                |              |                |              |                |              |                |              |              |

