### **Visit 4**

The following will be performed:

- Body measurements including weight and waist circumference (5.5.8, 5.5.9)
- Vital signs (5.5.7)
- Adverse events (6)
- Medical history/medication changes (5.5.4)
- Dietary counselling (control arm only) with dietitian (5.5.3)
- Diabetologist/Endocrinologist diabetes review (control arm only) with (5.5.1)
- EndoBarrier Implant (Treatment arm only) (5.5.2)
- Gastric and small bowel biopsies during EndoBarrier Implant (Treatment arm only) (5.5.2)

|                                                                                   |                                                                                                  |                                           |                                                             |                                                  |
|-----------------------------------------------------------------------------------|--------------------------------------------------------------------------------------------------|-------------------------------------------|-------------------------------------------------------------|--------------------------------------------------|
| [figure not shown] | Title:
EndoBarrier TM
Gastrointestinal Liner
Diabetes Trial | Protocol No:
Version 5.0 | Sponsor:
Imperial College
London | Date:
5th March 2018 |
|-----------------------------------------------------------------------------------|--------------------------------------------------------------------------------------------------|-------------------------------------------|-------------------------------------------------------------|--------------------------------------------------|

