## 5.5 Description of procedures and measurements

### 5.5.1 Diabetologist/Endocrinologist Diabetes Review

The standard medical therapy arm will be carried out in accordance with the guidelines of the American Diabetes Association (see figure 2 for summary algorithm). These guidelines have been chosen as they are applicable to an International audience and thus would adhere to the current best worldwide practice that would still be likely to be relevant when the results are published following study completion.

Diabetes reviews appointments with a Diabetologist/Endocrinologist will be performed with the control arm patients at visits 2, 4, 6, 7, 9, 11, 12, 13 and 15. Diabetes reviews appointments with a Diabetologist/Endocrinologist will be performed with the EndoBarrier arm patients at visits 2, 6, 7, 9, 11, 12, 13 and 15. Blood glucose concentrations obtained as part of study-scheduled routine blood tests will be used alongside self-measurements and self-reporting of blood glucose concentrations by patients or their GP's to adjust medication regimens. Home blood glucose meter readings will be indicated, as in routine clinical practice, when patients are clinically suspected or at risk of hypoglycaemic episodes (e.g. when commenced on sulphonylurea) or when glucose readings are required for further titration of therapy.

A summary of general recommendations for anti-hyperglycaemic therapy in type 2 diabetes patients have been outlined below (Figure 2) according to the American Diabetes Association (ADA) and the European Association for the Study of Diabetes (EASD).

All female patients will also be asked to report the last date of their menstrual period, the length of their cycle and the length of their menstruation (bleeding) at screening visit, visit 2, 4, 6, 7, 9, 11, 12, 13 and 15. This information will be used to ensure they are not pregnant and it will also help to monitor any changes in their menstrual cycle during the course of the study.

|                                                                                   |                                                                             |                                    |                                               |                                            |

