#### Delivery

The implant is delivered on a custom catheter fabricated from materials with a long history of biocompatibility (medical grade PEBAX and high density polyethylene tubing and PTFE-coated stainless steel wire). The sterile catheter is approximately 3 meters long to facilitate delivery of the implant through the mouth into the jejunum. The catheter is designed to be sufficiently flexible to track through the intestine without kinking. Implantation and removal of the EndoBarrier device requires fluoroscopic x-ray guidance to determine the position of the device. Videos and photos of

|                                                                                   |                                                                                                  |                                           |                                                             |                                                  |
|-----------------------------------------------------------------------------------|--------------------------------------------------------------------------------------------------|-------------------------------------------|-------------------------------------------------------------|--------------------------------------------------|
| [figure not shown] | Title:
EndoBarrier TM
Gastrointestinal Liner
Diabetes Trial | Protocol No:
Version 5.0 | Sponsor:
Imperial College
London | Date:
5th March 2018 |
|-----------------------------------------------------------------------------------|--------------------------------------------------------------------------------------------------|-------------------------------------------|-------------------------------------------------------------|--------------------------------------------------|

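### No pregnancy test is scheduled on the day of the X-ray-guided implant (Visit 4); the last scheduled one is at least 18 days old, or 4 to 24 days old in sub-group 1

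*Protocol*

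**What the plan says.** Section 5.5.6 of the protocol sets the testing rule for all women in the trial. Tests are "performed for females of childbearing potential at screening and at any time during the trial if a menstrual period is missed". In Table 2 the row "Urine dipstick and female pregnancy test (5.5.6)" carries a mark at Visit 1 and nowhere else. Women in sub-group 1 have further tests at Visits 3 and 8, before MRI (sections 5.5.6 and 5.6.7).

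The implant takes place at Visit 4. The Visit 4 list in section 5.4 contains "EndoBarrier Implant (Treatment arm only) (5.5.2)" but no pregnancy test. Section 5.5.2 states: "Implantation and removal of the EndoBarrier device requires fluoroscopic x-ray guidance to determine the position of the device".

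The other safeguards are:

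- Section 4.3 excludes "Females of childbearing potential who are pregnant, breast-feeding or intend to become pregnant or are not using adequate or reliable contraceptive methods", and section 4.4 requires withdrawal from treatment for pregnancy.
- Section 5.5.6 adds: "The use of adequate contraceptive methods will also be reinforced to each individual at screening and during each study visit".
- Section 5.5.1 has all women report the date of their last period, "the length of their cycle and the length of their menstruation (bleeding) at screening visit, visit 2, 4, 6, 7, 9, 11" and later visits. One stated purpose is to confirm that they are not pregnant.

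**The concern.** Visit 4 is the last point at which two exposures can both be prevented: the X-ray exposure, and exposure to a device for which section 5.5.6 reports no safety data in pregnancy. No test result from that day is required. The testing rule leaves the decision to a menstrual history, and no test is called for when the dates are unclear.

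The protocol's own practice points the other way. Sub-group 1 women are tested at each MRI visit and excluded if positive, although section 5.6.8 notes that none of the MR techniques uses ionising radiation. Women about to have fluoroscopy and a 12-month implant have no scheduled test that day.

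A pregnancy found after implant would generally lead to removal when safe (section 5.5.6), a second procedure that also uses fluoroscopy. The participant would count as a withdrawal after treatment start and would not be replaced (section 8.1). Drop-outs before Visit 4 can be compensated by further randomisation.

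**Working it through.** The protocol states no interval between test and implant, so there is no figure to reproduce. The interval follows from the visit windows in Table 2, read as all counted from one common day 0.

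**Inputs (Table 2)**

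- Visit 2: −28 ± 7 days, so day −35 to day −21.
- Visit 3: −14 ± 7 days, so day −21 to day −7.
- Visit 4: 0 ± 3 days, so day −3 to day +3.
- Visit 1: no time given. It precedes Visit 2, because randomisation follows screening and the arm is disclosed at Visit 2 (section 5.2).

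**Formula.** Shortest gap = earliest Visit 4 minus latest earlier visit. Longest gap = latest Visit 4 minus earliest earlier visit.

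| Interval | Shortest | Nominal | Longest |
|---|---|---|---|
| Visit 2 to Visit 4 | −3 − (−21) = 18 days | 28 days | 3 − (−35) = 38 days |
| Visit 3 to Visit 4 (sub-group 1) | −3 − (−7) = 4 days | 14 days | 3 − (−21) = 24 days |

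Outside sub-group 1 the last scheduled test is at Visit 1, which is no later than Visit 2. It is therefore at least 18 days old at implant and nominally more than 28 days old. There is no upper limit, because Visit 1 has no window.

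**Sensitivity to the anchor.** If Visit 4 itself defines day 0, Visit 2 lies 21 to 35 days before it and Visit 3 lies 7 to 21 days before it. The screening test is then at least 21 days old, and the conclusion is the same.

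**H. pylori positives.** Section 5.5.16 has these patients treated for a week and retested 4 weeks later, with Visit 2 repeated and no new pregnancy test listed. If the repeat falls at −4 weeks, the first Visit 2 was at about −8 weeks or earlier, so the screening test is nominally more than 8 weeks old.

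**What a Visit 4 test adds.** Let L be the days from conception until a test turns positive. The documents do not give L; assume it is equal for both tests. An earlier test on day t₀ covers conceptions up to t₀ − L. A test on day t₄ covers those up to t₄ − L. The difference is t₄ − t₀, the gap itself, whatever L is. Conceptions in the last L days before Visit 4 are missed either way.

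**Removal.** Visit 11 is at +12 months. The last scheduled test is then more than 12 months old, or 12 − 6 = about 6 months old in sub-group 1 (Visit 8).

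**The case against.** The strongest reply is that the protocol does check for pregnancy on the implant day. Section 5.5.1 asks all women for menstrual dates at Visit 4, and section 5.5.6 requires a test for a missed period. With regular, correctly reported cycles, and a test that turns positive at about the missed period (an assumption), this rule and a routine strip would find largely the same pregnancies. That stands. It means the newly covered window is measured against the last scheduled test, and the true gain over the whole protocol is smaller. It does not close the gap. The menstrual question sits in the diabetes review section, and at Visit 4 that review is for the control arm only. The wording covers device-arm women, but who asks them is not stated.

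Second, sections 4.3 and 4.4 already imply that a woman with a positive test would not be implanted. True, but those rules act only once a pregnancy is known.

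Third, the Visit 4 list is not a full theatre checklist. Section 5.5.2 sends patients through a pre-assessment unit, and section 1.5 refers to the Instructions for Use; either may add a test. Neither is shown, so such a test can be neither assumed nor ruled out.

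Fourth, a test before removal gains little. By Visit 11 the device exposure has happened. Section 5.5.6 regards endoscopy as safe in pregnancy. Section 6.10 gives a mean X-ray time of 1.5 minutes (range 0–15) for removal against 7 minutes (range 1–20) for insertion in an earlier study. This is accepted, so that part is secondary.

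Finally, Table 2 and sections 5.4 and 5.5.6 agree with one another, so this is a design choice and not a contradiction. Agreed.

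**Conclusion.** The point holds as a weakness in the safety schedule that should be corrected. No pregnancy test is scheduled at Visit 4. The last scheduled test is at least 18 days old at implant (nominally more than 28, no stated maximum), or nominally 14 days old (4 to 24) in sub-group 1. These figures rest on windows counted from a common day 0 and on Visit 1 being no later than Visit 2.

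The day counts measure the age of a test, not a risk. Existing safeguards cover part of the window, and the net benefit lies in misreported or unclear cycles. Its size cannot be derived: the protocol gives neither the number of women concerned nor a fetal dose. The 9 mSv it does state is the maximum effective dose for implant and explant combined. Confidence is medium, chiefly because local theatre practice and the Instructions for Use are not shown. Sample size, power and type I error are unaffected.

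**What to change.** Amend Table 2 and sections 5.4 and 5.5.6. Add a urine pregnancy test at Visit 4 for device-arm women of childbearing potential, keeping the existing exemptions in section 5.5.6. The result is to be read before fluoroscopy, with no implant if it is positive.

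Secondarily, add the same test before Visit 11 or any early removal. A positive result there would lead to an individual decision on timing and X-ray use.

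The cost is one urine strip per procedure, at a visit the woman already attends, plus the amendment. The downsides are an occasional postponed implant and a harder timing decision at Visit 11, since the CE mark covers 12 months of implantation. Very early pregnancies may still be missed.
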